### Interventions

Contrast between the interventions is found in their theoretical basis and point of engagement where the treatment focuses on. Graded Exposure uses principles from classical conditioning and cognitive therapeutic techniques to systematically reduce pain-related fear and catastrophic thinking in adolescents with chronic pain [42]. Graded Activity uses principles of operant conditioning, resulting in rewarding healthy and age adequate daily functional activities performed by the adolescent and a stepwise increase of the adolescent’s activity levels [42].

Parents are present and are invited to participate in both the intervention and control condition. However, in the intervention condition (MRP), parents receive additional 3 group meetings (the parent module) with the treatment team (Table 1). Meaning that in the MRP parents are involved in the treatment of their adolescent in two ways. They are both present and participate during treatment of their child, but additionally they participate in a separate parent module.

Both treatments are provided by a multidisciplinary treatment team, including a consultant in rehabilitation medicine, a physiotherapist or occupational therapist and a psychologist/behavioural therapist.

#### Intervention group

In Table 1 the elements of the three modules of the MRP are described. Graded Exposure aims to increase healthy behaviour by systematically and gradually exposing adolescents to fear provoking activities and movements. Starting point for this approach is a personal hierarchy of activities feared by the adolescent. The Photograph series of Daily Activities – Youth (PHODA-Youth) [27] is used as a standardized procedure to build these personal hierarchies. All therapists in the MRP condition received training on the principles of Graded Exposure therapy and the treatment protocols, consisting of a workshop and a 3-day training provided by skilled trainers (with 3 to >15 year experience in Graded Exposure therapy). Administration of the PHODA-Youth was part of the 3-day training.

Adolescents in the intervention condition MRP receive a graded exposure module (7 weeks) or a combination module (15 weeks) with training and graded exposure. Their parents receive a parent module (3 meetings). Adolescents with CMP receive the graded exposure module. If an adolescent is additionally identified (Brighton criteria including Beighton score, will be used [29, 32, 43]) as having pain complaints related to joint hypermobility (HMS), the combination module will be offered. All parents in the MRP condition are offered the parent module, which is organised in the evening hours.

#### Control group

Currently, treatment of adolescents with chronic pain in a rehabilitation setting consists of multidisciplinary treatment based on the principles of Graded Activity. Table 2 presents the main treatment elements of GA. GA aims to increase healthy behaviour by employing operant learning principles such as encouraging desired behaviours [42]. The treatment consists of a time contingent and stepwise increase in the level of functioning, despite complaints of pain [44]. Duration of the care as usual treatment varies between 9 and 16 weeks. This variation exists because each collaborating treatment centre has developed its own specific treatment protocol, also depending on the practical and logistic possibilities of the treatment centre. Content of the treatment programmes is generally similar and principal discriminative from the content of the experimental intervention (MRP).

**Table 2 Tab2:** Control group: Care as Usual, description of the treatment

*Phase 1 Inventory of the problem* • Anamnesis • Estimation of motivation for rehabilitation treatment • Physical examination • Identification of maintaining factors for the pain problems • Analysis of activities *Phase 2 Problem analyses* • Ordering information from inventory • Providing an explanatory model for the pain problem • Treatment plan *Phase 3 Education* • Exploring willingness to change behaviour • Changing behaviour despite pain *Phase 4 Choosing activities* • Choosing activities on a functional level • Determining treatment goals (SMART) *Phase 5 Determining baseline (Pain contingent functioning)* • Determining baseline level of functional activities (min 3–5 measurement moments) *Phase 6 Determining goal and scheme to increase activity* • Starting level below baseline • Scheme for time contingent increase in activities • Establishing treatment goals *Phase 7 Executing scheme* • Time contingent increase of activities • Encouragement of successful behaviour • Generalization at home and school *Phase 8 Generalization and evaluation* • Applying in daily situations • Evaluation of treatment	

### Outcome measures

PedIMMPACT recommendations were followed when choosing outcome domains and in the selection of measurement instruments for this study [45]. Details of measurement instruments can be found in Table 3. Assessments will be performed at baseline (before start of treatment) and at 2, 4, 10 and 12 months after start of treatment. Primary outcome measure is adolescent’s functional disability (FDI) [46, 47]. Secondary outcome measures are adolescent fear of pain (FOPQ-C) [48], perceived harmfulness (PHODA-Youth) [27], pain catastrophizing (PCS-C) [49, 50], pain intensity (VAS) [51], depressive symptoms (CDI) [52] and pain specific quality of life (QLA-CP) [53], and parent perceived functional disability (FDI-P) [46, 47], fear of pain (FOPQ-P) [48], pain catastrophizing (PCS-P) [50], adult responses to children’s symptoms (ARCS) [54].

**Table 3 Tab3:** Primary and secondary outcome measures^a^

Primary outcome	Measurement instrument	Time points of measurement
Functional disability [46, 47]	Functional Disability Inventory (FDI)	Baseline, 8 weeks, 16 weeks, 10 and 12 months
	Self-report measure for perceived difficulty in performing activities at school, at home and in recreational or social interactions.	
	15 Items rated on a five-point scale (0–4). Total scores range 0–60 with a higher scores indicating greater disability.	
	Valid and reliable measure for assessing pain related disability in adolescents.	
ᅟ	ᅟ	ᅟ
Secondary outcomes	Measurement instrument	Time points of measurement
Fear of pain [48]	Fear of Pain Questionnaire (FOPQ-C)	Baseline, 8 weeks, 16 weeks, 10 and 12 months
	Self-report measure to assess pain-related fear in adolescents with chronic pain. 24 items rated on a five-point scale (0–4). Total scores range 0–96 with a higher score indicating more fear. Consists of subscales 1) Fear of Pain and 2) Avoidance of activities.	
	Psychometric properties of the English version are good.	
Perceived harmfulness [27]	PHODA-Youth	Baseline, 8 weeks, 16 weeks, 10 and 12 months
	Measures perceived harmfulness of physical and social activities and can be used to create a hierarchy of fearful activities.	
	51 photographs are rated on a scale 0–10 (steps 0.1). The higher a photo is ranked, the more harmful the adolescent thinks executing the activity is. Consists of subscales 1) activities of daily living, 2) intensive physical activities and 3) social activities.	
	Psychometric qualities are good.	
Pain Catastrophizing [49]	Pain Catastrophizing Scale (PCS-C)	Baseline, 8 weeks, 16 weeks, 10 and 12 months
	Self-report measure of catastrophic thinking about pain. Frequency of feelings and thoughts adolescents may experience when they are in pain are measured.	
	13 items rated on a five-point scale (0–4). Total scores range 0–52 with higher scores indicating more catastrophic thinking. Consists of subscales 1) Rumination, 2) Magnification, and 3) Helplessness. Reliability and validity are good.	
Depressive symptoms [52]	Child Depression Inventory (CDI)	Baseline, 8 weeks, 16 weeks, 10 and 12 months
	Self-report measure of depressive symptoms in children and adolescents.	
	27 items rated on a three-point scale (0–2). Total scores range 0–54 with higher scores indicating more depressive symptoms. Consists of subscales 1) Negative mood, 2) Interpersonal problems, 3) Ineffectiveness, 4) Negative self-esteem, and 5) Anhedonia.	
	Dutch version demonstrates good reliability and validity.	
Pain specific quality of life [53]	Quality of Life in Adolescent with Chronic Pain (QLA-CP)	Baseline, 8 weeks, 16 weeks, 10 and 12 months
	Self-reported pain-specific quality of life measure for adolescents with chronic pain.	
	44 items in 6 domains, 1) Psychological functioning, 2) Functional status, 3) Physical status, 4) Social functioning, 5) Satisfaction with life in general, and 6) Satisfaction with health. A high score on each domain of the questionnaire represents a better quality of life.	
	Internal consistency and construct validity have shown to be adequate.	
Pain Intensity [51]	Visual Analogue scale (VAS)	Baseline, 8 weeks, 16 weeks, 10 and 12 months
	Self-report measure of pain intensity. Sliding scale where the ends of the line represent the extreme limits of pain intensity (no pain at all and worst pain imaginable). Average VAS score is taken of pain at this moment, worst and least pain in last week.	
	Reliable method in children above 8 years old. Sound psychometric properties and clinical utility.	
Parent perceived Functional Disability [46, 47]	Functional Disability Inventory – Parent report (FDI)	Baseline, 8 weeks, 16 weeks, 10 and 12 months
	Measure of parent perceived functional disability of their child.	
	15 items rated on a five-point scale (0–4). Total scores range 0–60 with higher scores indicating greater parent-perceived difficulty in performing activities.	
Parent perceived Fear of Pain [48]	Fear of Pain Questionnaire – Parent report (FOPQ-P)	Baseline, 8 weeks, 16 weeks, 10 and 12 months
	Parent proxy report measure to assess parents perception of their childs pain-related fear experience.	
	23 items rated on a five-point scale (0–4). Total scores range 0–92 with higher scores indicating a higher parent perceived fear. Consists of subscales 1) fear of pain, 2) avoidance of activities, and 3) School avoidance.	
	Psychometrically sound measure with strong internal consistency, good construct and criterion validity.	
Parental Pain catastrophizing [50]	Pain Catastrophizing Scale – Parent report (PCS-P)	Baseline, 8 weeks, 16 weeks, 10 and 12 months
	Measures parental catastrophizing about their child’s pain.	
	13 items rated on a five-point scale (0–4). Total scores range 0–52 with higher scores indicating more catastrophic thinking by the parents.	
	Psychometric properties are good to very good.	
Adult response to children’s symptoms [54]	Adult response to children’s symptoms scale (ARCS)	Baseline, 8 weeks, 16 weeks, 10 and 12 months
	Parent self-report measure of a range of parental responses to pain of their child.	
	29 items rated on a five-point scale (Never-always). Consists of subscales 1) Protective responses, 2) minimizing responses (criticizing or downplaying the pain) and 3) monitoring/encouraging responses (encouraging activity while monitoring symptoms)	
	Valid instrument for assessing parents’ responses to children’s pain for diverse chronic pain symptoms.	
Other study parameters	Used in economic evaluation and process evaluation	
Costs (economic evaluation) [55]	Cost diary	After treatment each month until month 12.
	Health care utilization, school absence and productivity losses are recorded.	
Generic health related quality of life (economic evaluation) [56]	EQ-5D-Y	Baseline, 8 weeks, 16 weeks, 10 and 12 months
	Generic self-report measure of health related quality of life.	
	5 Items, scored on three levels: no problems, moderate problems, severe problems. Contains domains 1) mobility, 2) self-care, 3) usual activities, 4) pain/discomfort, and 5) anxiety/depression. 1 visual analogue scale to rate their own health between 0 and 100 (best health state).	
Satisfaction/patient centeredness (Process evaluation) [58]	Giving Youth A Voice Questionnaire (GYV-20)	16 weeks
	The instrument has 4 themes, 1) supportive and respectful relationships, 2) Information sharing and communication, 3) Supporting independence and 4) Teen-centred service. Each item is formulated as a question, starting with ‘How much do the people who work with you…’ and then a description of a specific action or behaviour of the health care professional is given. Response options range from 1–7, with a ‘not applicable’ category added. Scale scores can be calculated as the mean of the ratings for the items in the scale.	
Satisfaction/family centeredness (Process evaluation) [59, 60]	Measure of Processes Of Care – Parent form – Short form (MPOC-P-20)	16 weeks
	20 items, scored on a scale 1–7. Consists of 5 scales, 1) Enabling and Partnership, 2) Providing General Information, 3) Providing Specific Information about the Child, 4) Coordinated and Comprehensive Care for the Child and Family and 5) Respectful and Supportive Care. Responses to each item are converted to a mean for each scale. No total score can be calculated.	
Treatment expectations of children (Process evaluation) [61]	Credibility/Expectancy Questionnaire (CEQ-Adolescent)	Baseline
	On the 11 items (5 on credibility, 6 on expectancy) can be answered on a 9-point scale from ‘totally not’ to ‘totally’. Total scores are a sum score of the individual items and ranges from 11 to 99.	
Treatment expectations parents (Process evaluation) [61]	Credibility/Expectancy Questionnaire (CEQ-Parent)	Baseline
	On the 11 items (5 on credibility, 6 on expectancy) can be answered on a 9-point scale from ‘totally not’ to ‘totally’. Total scores are a sum score of the individual items and ranges from 11 to 99.	
Joint Hypermobility Syndrome (HMS) [29, 32, 43]	Birghton Criteria	Baseline
	To identify adolescents with HMS the Brighton criteria, including a Beighton score will be used. A cut-off value of ≥5 will be used for hypermobility.	

^a^Not for all measures detailed information about reliability and validity was available

#### Other study parameters

Demographic variables will be measured at baseline. These variables include age, sex, educational level and school absence, family composition, ethnic background. Variables related to chronic pain that will be measured include: onset and duration of pain complaints, location of pain complaints, course of the complaints, and (if applicable) medication use.

#### Costs measurement

To evaluate the economic consequences, the intervention costs, other health care costs, patient and family costs, and productivity losses will be assessed. Patient and family costs include out-of-pocket costs, such as costs for informal care and extra expenses. Productivity losses (for adolescents and parents) are based on the days absent from work or school because of the pain.

At baseline, total costs will be inventoried 3 months retrospective. During the trial period (12 months) monthly cost-diaries will be used after the end of treatment. For addressing cost-effectiveness of interventions, the cost-diary method might be a successful method [55]. Both the parents and the adolescents will be asked to provide information about health care utilization and school absenteeism/productivity losses. If the adolescents are 18 years or older, they may choose to fill out the cost diary themselves, below 18 years it is recommended they complete the cost diary together with their parents.

Generic health related quality of life was measured with the EQ-5D-Y [56]. The EQ-5D-Y is a self-report measure of health related quality of life. QALY’s can be calculated by means of the applying a tariff to obtain a weighted health state index. The adult tariff will be used for the Youth-version of the questionnaire, since no youth-tariff is available.

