## Methods

### Study design and participants

A two group pragmatic randomized controlled trial is undertaken with adolescents with CMP, with follow-up assessment at 2, 4, 10 and 12 months after start of treatment. Adolescents will be allocated to either intervention (MRP) or control (CAU) with a ratio 1:1. Patients who receive an indication for outpatient rehabilitation treatment will be invited to participate and will be randomized to either usual care (CAU) or the intervention (MRP) after informed consent is obtained. Parents will be asked to participate as well.

Estimates for the calculation of the sample size are based on the primary outcome measure, the Functional Disability Inventory (FDI). An average FDI total score of 23 (average score obtained from adolescents that were treated at the Maastricht University Medical Centre in the year before the start of this study), a standard deviation of 9.2 and an expected mean difference between intervention and control condition of 5 points on the total FDI-score were used. A difference of 5 points equals approximately a 25 % difference in mean FDI scores between intervention and control group.

Given α = 0.05, two sided testing, a power of 80 %, and anticipating 15 % loss to follow-up, a sample size of 62 participants per trial-arm was calculated. For two trial arms, this results in a total sample size of *N* = 124.

Adolescents will be recruited from 4 centres in The Netherlands: Maastricht University Medical Centre/Adelante, Laurentius Hospital Roermond, Revant Rehabilitation centre Breda and Rijndam Rehabilitation Centre in Rotterdam. Both treatments offered are embedded in the daily care process in each treatment centre, with an inclusion period of 1.5 years. Ethical approval for this trial was granted by the Medical Ethics Committee Academic Hospital Maastricht/Maastricht University, the Netherlands, NL47323.068.13/METC13-3-062.

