#### Economic evaluation

In the economic evaluation costs and effects of the intervention condition (MRP) and the control condition (CAU) will be calculated and compared, using a societal perspective. Total costs will be estimated using a bottom-up approach, where information on each element of service use is multiplied by an appropriate standardized unit cost and summed to provide and overall total cost. For the cost valuation, standardized cost prizes will be used from the Dutch manual for cost analysis in health care research [63]. Productivity losses will be calculated based on the Human Capital Approach.

At baseline resource use prior to the study will be measured, to allow this use as a covariate in the analysis, which enables correction for possible cost differences at baseline [64]. Cost per patient year (= participant year) will be calculated.

Intended, both a cost-effectiveness analysis (CEA) and a cost-utility analysis (CUA) will be performed. For the CEA the cost-effectiveness ratio will be stated in terms of cost per 5 points of improvement on the Functional Disability Inventory (FDI). For the CUA the cost-utility ratio will be stated in terms of cost per Quality Adjusted Life Year (QALY) gained, as measured by the EQ5D-Y [65]. Bootstrap re-sampling techniques will be used to test for differences and uncertainty in cost and effects between MRP and CAU.

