Adolescents aged 12–21 years old are eligible to participate in the trial. Paediatric rehabilitation services are in principle provided up to the age of 18 years old. Most studies on treatments for adolescents include participants up to the age of 18 years old. The range of 12–21 years was chosen according to Kaplan’s [72] definition of adolescent life stage, starting with early adolescence at 12 years old, ending of late adolescence at 21 years old. Furthermore, research has shown that up to the age of 21 years, brain functions are still developing [73]. Therefore, interpretation of cognitive and behavioural processes can still be sensitive to change and can best be seen in to context of adolescence instead of adulthood. Additionally, in the Netherlands only 20 % of the 15–20 year olds are part of the working population, so for the largest part of this age group, their daily social and physical activities are more in line with the school-attending adolescents than with the working adult population.

To our knowledge, 2B Active is one of the first studies performing an economic evaluation on outpatient treatment and follow up, focussing both on the cost of the intervention itself and on patient and family costs. No measurement instrument existed that measured both adolescent and parent costs of the rehabilitation trajectory and follow-up. Therefore, a cost diary was developed to measure both medical consumption and productivity losses (work and school absenteeism) after completion of the rehabilitation program.

To summarize, several design choices that have been made may influence the balance between internal validity and external validity of the study. By studying the new intervention in a pragmatic way and in the setting in which the MRP treatment is intended to be offered, the results will be more generalizable to daily practice of rehabilitation care. Including a heterogeneous group of patients and analysis according to ITT may lead to results that are not over-estimated since real practice daily difficulties are incorporated in the trial results.

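### Non-intervention societal costs go unrecorded during treatment, because the cost diary opens only when treatment ends, and the diary window varies from 36 to 45 weeks by arm, module and centre

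*Protocol article*

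**What the plan says.** Three places in the protocol article agree on when the diary runs.

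- Costs measurement: within the 12-month trial period, "monthly cost-diaries will be used after the end of treatment".
- Table 3, under Outcome measures: "After treatment each month until month 12".
- Discussion: the diary was developed to capture "medical consumption and productivity losses (work and school absenteeism) after completion of the rehabilitation program".

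The 12-month clock runs from the start of treatment. Study design and participants describes a trial "with follow-up assessment at 2, 4, 10 and 12 months after start of treatment".

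Treatment length differs by arm, module and centre. MRP is a "graded exposure module (7 weeks) or a combination module (15 weeks") (Intervention group). For the control arm, "Duration of the care as usual treatment varies between 9 and 16 weeks", because each centre has its own programme (Control group).

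Costs measurement lists the cost of the intervention as its own category, apart from other care, family expenses and lost production. It also sets a baseline inventory looking back 3 months. Under Economic evaluation, "costs and effects of the intervention condition (MRP) and the control condition (CAU) will be calculated and compared, using a societal perspective". That section also promises a cost per participant year, a cost per 5 FDI points and a cost per QALY. Table 3 schedules FDI and EQ-5D-Y at baseline, 8 weeks, 16 weeks, 10 months and 12 months.

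**The concern.** A societal cost per participant year needs every cost category observed over that year. Here the retrospective inventory ends at baseline and the diary opens when treatment ends. Nothing is stated to record other care, school absence or lost work in between. School absence appears elsewhere only as a baseline variable (Other study parameters).

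The diary also opens at a point after randomisation that depends on the allocated treatment, and closes at a fixed date. The amount of cost observation is thus partly a consequence of allocation. QALYs and FDI change cover the treatment period while these costs do not, so the numerator and denominator of each ratio have different horizons.

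The secondary aim of comparing cost-effectiveness and cost-utility is at stake. This is a stated rule for collecting data. Followed as written, it leaves a gap that no later analysis plan can recover.

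**Working it through.** **Inputs, all from the protocol article.** Treatment length d: 7 weeks (graded exposure) or 15 weeks (combination), from Intervention group; c = 9 to 16 weeks (CAU), from Control group. These span 7 to 16 weeks, which agrees with the overall range in the Abstract. The horizon is 12 months from the start of treatment, taken as 52 weeks. The article gives no figure for the diary window itself.

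**Step 1. Diary window = 52 - d; uncovered share = d/52.**

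| Group | d (weeks) | Window (weeks) | Year uncovered |
|---|---|---|---|
| MRP, graded exposure | 7 | 45 | 13.5% |
| MRP, combination | 15 | 37 | 28.8% |
| CAU, shortest | 9 | 43 | 17.3% |
| CAU, longest | 16 | 36 | 30.8% |

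**Step 2. Difference between the randomised arms.** Let p be the share of MRP patients on the combination module. The article does not give p. Mean MRP length is m = 7(1 - p) + 15p = 7 + 8p. The MRP window minus the CAU window is (52 - m) - (52 - c) = c - m.

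- Lowest: p = 1, c = 9 gives 9 - 15 = -6 weeks, and -6/43 = -14%.
- Highest: p = 0, c = 16 gives 16 - 7 = +9 weeks, and 9/36 = +25%.

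With CAU at its midpoint of 12.5 weeks (an assumption; window 39.5 weeks):

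| p (assumed) | m | c - m | % of 39.5 |
|---|---|---|---|
| 0 | 7.0 | +5.5 | +13.9% |
| 0.40 | 10.2 | +2.3 | +5.8% |
| 0.55 | 11.4 | +1.1 | +2.8% |
| 1 | 15.0 | -2.5 | -6.3% |

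The values 0.40 and 0.55 borrow the hypermobility prevalence of 40 to 55% quoted in the Background. Hypermobility is not the same as the hypermobility syndrome that decides the module, so they are illustrative only.

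**Step 3. Does annualising solve it?** Let w be the weekly non-intervention cost after treatment and kw the weekly cost during treatment.

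- True 12-month cost: w(52 - d) + kwd.
- Raw diary sum: w(52 - d), which is short by kwd.
- Annualised diary cost: 52w, in error by wd(1 - k).

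Annualising is exact only if k = 1. If w and k are the same in both arms, the error left in the MRP minus CAU comparison is (m - c)w(1 - k). If k differs by arm, there is a further error. The diary as scheduled gives no information on k.

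**Step 4. Is k = 1 a safe assumption?** Table 1 gives 1 + 1 + 12 × 1 = 14 hours of adolescent sessions for graded exposure and 1 + 1 + 16 × 2 + 6 × 1 = 40 hours for the combination module. Parents are present during treatment in both arms (Interventions). Treatment weeks may therefore differ from later weeks, and between modules, in what families spend and lose. The article does not say by how much.

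**The case against.** **The treatment period is not wholly missing.** A reader might infer that treatment-period costs drop out of the comparison altogether. They do not: intervention costs are a separate category, and Economic evaluation values service use bottom-up. Only the non-intervention part lacks a source. This stands.

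**The windows need not differ much between arms.** A reader might set the 7-week module against CAU (45 weeks v 43 to 36) and conclude that costs will show a spurious difference of 5% to 25%. The documents do not support that. The randomised comparison is all of MRP against all of CAU, the duration ranges overlap, and minimisation balances the arms by centre. The upper figure needs no combination patients and a 16-week programme for every CAU patient. It also assumes that raw diary sums are compared. This stands too.

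**A cost per participant year may imply annualising.** If it does, unequal windows alone create no difference when weekly costs are constant. The calculation could properly sit in a fuller document. This answers the window-length problem but not the gap, since the rate for the uncovered weeks would be assumed.

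**Productivity loss is defined as absence because of pain.** An earlier diary would not clearly capture time taken off to attend sessions, and the MRP parent meetings are held in the evening. This limits one type of missed cost. Pain-related absence and other care during treatment remain unrecorded.

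**Month 12 might mean 12 months after treatment ends.** The windows would then be equal, but treatment would still be uncovered. Study design and participants, Outcome measures and Costs measurement all point to the start of treatment.

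**Conclusion.** The point holds for non-intervention societal costs. As written, they have no stated source for 7 to 16 weeks after treatment starts (13% to 31% of the year), and diary windows range from 36 to 45 weeks. The gap rests only on the stated diary rule and treatment lengths, with 12 months taken as 52 weeks from the start of treatment.

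The difference between arms is less certain. It lies between -6 and +9 weeks (-14% to +25% of the CAU window), and its sign depends on the module mix and on CAU length by centre, neither of which is given. A reader might go on to infer that incremental cost and both cost-effectiveness ratios are biased in a known direction. The documents do not show that.

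The rule should be changed for the economic evaluation, because the lost data cannot be recovered later. The primary FDI analysis is untouched.

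**What to change.** Start the existing monthly diary at the start of treatment in both arms and run it to month 12. Non-intervention costs, intervention costs and QALYs then share one 12-month horizon, and observation time no longer depends on allocation. Costs measurement, the Table 3 entry and the Discussion should be changed together.

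For families already past the start of treatment:

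- Keep all recorded diary data.
- State how the uncovered treatment weeks are handled, including any assumption that they cost the same as later weeks.
- Report a comparison over the window common to all (week 17 to month 12, 52 - 16 = 36 weeks) plus intervention costs, as a sensitivity analysis only. As the main analysis it would discard recorded costs, for example weeks 8 to 16 for graded exposure, and widen the mismatch with 12-month QALYs.
- State that treatment-period societal costs are not fully observed.

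**Cost.** Two to four more diaries per family (7 to 16 weeks at 52/12 = 4.3 weeks a month is 1.6 to 3.7 months), on a form already in use, with a small amendment and somewhat more respondent burden.
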